### Outcome measures and data collection

Data will be collected using self-reported questionnaires translated into the official language of each country. Validated translations will be used. When needed, the questionnaire will be translated with the forward-backward translation technique [30] and tested in each setting after being reviewed and adapted. Before the start of the study, questionnaires will be pilot-tested in all participating. The instruments used to measure the outcomes are described below.

Patient-reported outcomes to evaluate trial effectiveness includes HRQoL, intensity of symptoms, functional status, emotional distress, perceived quality of care and adherence to treatment. HRQoL is measured with the EQ-5D-5L instrument [31], which includes: mobility, self-care, usual activities, pain/discomfort and anxiety/depression. Intensity of symptoms is measured with the Palliative Care Outcome Scale (POS) [32]. The POS measures patients’ physical, psychological, emotional and spiritual symptoms, and is suitable for use in both specialist palliative care and non-specialist palliative care settings. Functional status is measured via the Palliative Performance Scale Version 2 (PPSv2) that includes five domains: ambulation, activity & evidence of disease, self-care, intake and conscious level [33]. Emotional distress is assessed with the Hospital Anxiety and Depression Scale (HADS) among patients [34]. It is a two-dimension scale developed to identify depression and anxiety among physically ill patients and the general population valid at hospital and in community settings. Perceived quality of care is assessed through a 5-point Likert scale related to communication, information provided, personalized care, family-centred and overall satisfaction. Adherence to treatment is assessed through the Medical Outcomes Study (MOS) [35].

Emotional distress and perceived quality of care will also be assessed among relatives or informal caregivers. In addition, caregiving burden will be measured among relatives or informal caregivers through the brief version of Zarit Burden Interview (ZBI) [36]. ZBI aims to evaluate the perceived impact of providing care on aspects such as the caregiver’s health, personal and social life, financial situation, emotional wellbeing and interpersonal relationships [37, 38].

For the purpose of the cost-effectiveness analyses, three categories of costs will be measured: the intervention costs, other healthcare costs and informal care costs. The intervention costs concern the resource units consumed (e.g. minutes spent by health and social care professionals, diagnostic procedures and consumables) and their unit costs, which will be collected by interviewing professionals as well as from Patient- or Administrative Data Management Systems. Special attention will be paid to overhead costs as they represent between 35 and 40% of intervention costs [39]. Other healthcare costs will be measured with the Medical Consumption Questionnaire (MCQ) [40], which will be completed by patients. The MCQ includes questions related to frequency of visits to healthcare professionals, hospital’s accident and emergency department and frequency and duration of hospital admissions. Informal care costs will be determined by the number of hours taking care of the patient with corresponding hourly productivity costs (Valuation of Informal Care Questionnaire (VICQ) [40]).

In terms of implementation, healthcare professionals involved in the implementation of the interventions will be invited to participate in personal interviews, focus groups and to complete questionnaires with a 5-point Likert scale. Items of those interviews and questionnaires are based on the Consolidated Framework for Implementation Research (CFIR). This framework guides diagnostic assessments of implementation context, evaluates implementation progress and helps explain findings in studies or quality improvement initiatives [41]. Both qualitative and quantitative information regarding receptivity, potential barriers and facilitators to implement the intervention will be gathered.

The baseline questionnaire also includes items regarding the socio-demographic characteristics of the patients, relatives/informal caregivers and healthcare professionals (see Table 2). Patients’ medical histories are also included in the baseline questionnaire. Table 3 presents the different measures to be used among the different end-users involved in the randomized controlled trials.

**Table 2 Tab2:** Socio-demographic and general characteristics

Variables	End-user
Age	Patient, informal caregiver, healthcare professionals
Sex	Patient, informal caregiver, healthcare professionals
Marital status	Patient
Level of education	Patient, informal caregiver, healthcare professionals
Ethnic background	Patient, informal caregiver
Professional category	Patient, informal caregiver
Relationship with the patient	Informal caregiver
Caregiving skills	Informal caregiver
Years of experience in caregiving	Informal caregiver
Preferences for place of care	Patient, informal caregiver, healthcare professionals
Preferences for place of death	Patient, informal caregiver, healthcare professionals
Active diagnosis (main diseases)	Patient
Time since initial diagnosis (main diseases)	Patient
Number of prescribed drugs	Patient
Type of prescribed drugs	Patient
Position	Healthcare professionals
Years of experience in general healthcare practice	Healthcare professionals
Years of experience in palliative care	Healthcare professionals
Previous training in palliative care	Healthcare professionals

**Table 3 Tab3:** Indicators of the feasibility, effectiveness and costs of the intervention

End user	Outcomes	Instrument	Moment
Patient	Health-related quality of life	EQ-5D-5L	T0, T1, T2, T3, T4
	Intensity of symptoms	POS	T0, T1, T2, T3, T4
	Functional status	PPSv2	T0, T1, T2, T3, T4
	Emotional distress	HADS	T0, T1, T2, T3, T4
	Quality of care	Short set of items	T0, T1, T2, T3, T4
	Other healthcare costs	MCQ	T0, T1, T2, T3, T4
	Adherence to treatment	MOS	T1, T2, T3, T4
Informal caregivers/ Relatives	Health-related quality of life	EQ-5D-5L	T0, T1, T2, T3, T4
	Emotional distress	HADS	T0, T1, T2, T3, T4
	Caregiving burden	Brief ZBI	T0, T1, T2, T3, T4
	Informal care costs	VICQ	T0, T1, T2, T3, T4
	Quality of care	Short items	T1, T2, T3, T4
Healthcare professionals	Feasibility, acceptability, adoption, appropriateness of the intervention	CFIR-based interview and questionnaire	T0, T1, T2, T3, T4
	Fidelity	Short set of questions based on the interventions’ components	T1, T2, T3, T4
	Intervention costs	Uniform reporting template; interview	T1, T2, T3, T4

### Data management and statistical analysis

The University of Valencia (UVEG) and the Erasmus Medical Center (Erasmus MC) are responsible for the analysis and reporting. UVEG, Erasmus MC and together with all clinical sites are responsible for the data manegement. All data will be gathered through the CASTOR eCRF system, which will be made available to the consortium.

Descriptive statistics will be carried out to summarize characteristics of participants in each clinical site and in the total study population. Tests for normal distribution of the continuous outcome measures will be performed using the Kolmogorov–Smirnov test. The outcome measures will be compared within each group (intervention group and control group) at different measurement times (i.e. T0-T1; T1-T2; T2-T3; T3-T4; T1-T4; T0-T4, etc.). A multilevel modelling approach will be used to examine differences in the outcome measures between the intervention and control group, taking into account the clustering effects at the clinical site level. The relationship between the outcome measures and independent variables will be assessed using Pearson correlation (for continuous variables) and Pearson Chi-square test (for categorical variables). Comparison between the intervention group and the control group at each evaluation moment will be conducted by including an interaction between the treatment groups and time in the multilevel model.

The cost-effectiveness analysis will be conducted from a societal perspective and on a within-trial horizon. The incremental cost-effectiveness ratio (ICER) will be calculated and the degree of uncertainty for costs and effectiveness and the cost-effectiveness ratio will be examined on the ICER by using non parametric bootstrapping. In addition, an acceptability curve will be generated to indicate the probability that the intervention has lower incremental costs per quality adjusted life year (QALY) gained than various thresholds for the maximum willingness to pay for an extra QALY.

In all cases, *p*-values < 0.05 will be considered statistically significant. All analyses will be carried out using the statistical package SPSS v26 or similar statistic software packages.

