## Aims and objectives

Within the InAdvance project at four locations a randomized trial will be performed lasting 18 months after the first intervention. In Valencia (Spain), Amadora (Portugal), Thessaloniki (Greece) and Highlands (UK) a novel model of palliative care will be implemented by integrating personalized pathways for palliative care that starts at an early stage of complex chronic conditions for older people (≥60 years old). The objective of our study is to evaluate acceptability, feasibility, effectiveness and cost-effectiveness of the novel model of palliative care in patients with chronic conditions.

In terms of effectiveness, self-reported outcome measures will be assessed with regard to both patients and informal caregivers/relatives to analyze the impact of the intervention on their wellbeing. The cost-effectiveness evaluation will assess whether there is ‘value for money’ and cost savings derived from the intervention. Finally, the implementation of the interventions process will be assessed at several times with the involvement of key healthcare professionals to identify facilitators and barriers of the implementation of the interventions.

We hypothesize that patients will have improved or maintained HRQoL and alleviated symptoms, and that multifaceted, complex needs including psychological, emotional and spiritual needs will be addressed. Informal caregivers/relatives will have improved or maintained HRQoL, increased social support, caring and coping skills and decreased caregiving burden. From the cost-effectiveness evaluation, we hypothesize that patients will have more efficient use of health care resources and contribute to a reduction of unnecessary costs.

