### Eligibility criteria and recruitment

Men and women of at least 60 years of age diagnosed with complex chronic conditions with a potential progressive course are eligible for the study, as well as their caregivers. A detailed description of the inclusion and exclusion criteria is shown in Table 1.

**Table 1 Tab1:** Inclusion and exclusion criteria related to patients for the needs assessment trail

Inclusion criteria	Exclusion criteria
• Participants with capacity to provide informed consent	• Individuals unable to provide written informed consent
• **Spanish, Portuguese and Greek sites:** No more than mild cognitive decline (≥18 points) on the Mini Mental State Examination (MMSE) [27] or up to 4 errors on the Pfeiffer Test [28] **UK site:** If the participant’s clinical record includes documented evidence of cognitive decline, participants should demonstrate no more than mild cognitive decline at screening (must score ≥ 18 points on MMSE)	• **Spanish, Portuguese and Greek sites:** Older adults diagnosed with cancer **UK site:** Older adults diagnosed with active cancer (excluding basal cell carcinoma and squamous cell carcinoma of the skin)
• Males and females	• Individuals currently enrolled on any other research which might interfere with the results and the procedure of the study
• Participants aged 60 years or older at the time of randomisation	• Individuals under the age of 60 years
• **UK, Portuguese and Greek sites:** Participants that have a clinical diagnosis of severe COPD or severe respiratory illness OR **UK site:** Participants with at least two co-occurrent chronic conditions (multi-morbidity), at least one of them being in a severe stage as determined by the patient’s clinical care team OR **Spanish and Portuguese sites:** Participants with at least two co-occurrent chronic conditions (multi-morbidity), at least one of them in a severe stage according to the specific criteria of severity and progression of disease of the NECPAL tool [29] OR **Greek site:** Participants that have a clinical diagnosis or severe respiratory illness and multi-morbidities (participants with severe heart failure, diabetes, lipidemia, hypothyroidism, or arthritis)	• Individuals who, in the opinion of the research team, may face physical or psychological risk/harm due to the invite participation or the enrolment on the study (i.e. subjects that are not aware of the severe prognosis, unstable clinical conditions)

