### Sample size considerations

Assuming a statistical power of 95% and an effect size of 0.20 regarding continuous outcome measures between intervention and control group with an alpha risk of 0.05, the sample size is estimated to be 320 participants; that is 80 at each of the four sites with 40 participants in the intervention group and 40 in the control group. In the study, for each patient participating in the study, it is expected to include one informal caregiver (e.g. a family member) who provides informed consent to join the study. Furthermore, for the formative evaluation, 10–15 health care professionals will be recruited to participate in the study at each study site.

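### Within-arm significance tests over many visit pairs stand beside the between-arm model, unlabelled, and the hypothesis names no comparator

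*Protocol article*

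**What the plan says.** Four places in the protocol article bear on this.

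- **Within-arm comparisons (Data management and statistical analysis).** "The outcome measures will be compared within each group (intervention group and control group) at different measurement times", with the pairs given as "i.e. T0-T1; T1-T2; T2-T3; T3-T4; T1-T4; T0-T4, etc". Six pairs are named and the list is left open.
- **Significance rule (same section, last paragraph).** For all analyses, p-"values < 0.05 will be considered statistically significant". No exception is made for the within-arm comparisons. The only sentence on descriptive statistics concerns participant characteristics.
- **Between-arm analysis (same paragraph as the within-arm comparisons).** "A multilevel modelling approach will be used to examine differences in the outcome measures between the intervention and control group", with clustering by site. The arms are compared at each visit by "including an interaction between the treatment groups and time in the multilevel model". Sample size considerations likewise bases the 320 participants on a between-arm effect.
- **Hypothesis (Aims and objectives).** "We hypothesize that patients will have improved or maintained HRQoL and alleviated symptoms". The hypothesis for informal caregivers uses the same improved-or-maintained form. Neither names Care-as-Usual as the comparator.

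**The concern.** A within-arm test asks whether one arm changed over time. It does not ask whether PCNA differs from Care-as-Usual. A significant change in one arm and a non-significant one in the other is not evidence that the arms differ. A non-significant change in the PCNA arm is not evidence that HRQoL was maintained, because it may only reflect limited power.

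This matters more here for two reasons. Participants are "diagnosed with complex chronic conditions with a potential progressive course" and are followed for 18 months, so a change shared by both arms is plausible. Also, a hypothesis of improvement or maintenance without a comparator describes the course of one arm, which is what the within-arm tests address. The valid and the invalid route to an effectiveness statement stand side by side at the same threshold, and nothing in the article says which one counts.

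**Working it through.** **Inputs from the article.** 320 participants randomised 1:1, so 160 per arm; threshold 0.05 (sidedness not stated; two-sided assumed); five visits, T0 to T4; outcomes and visits from Table 3.

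**Assumed, not in the article.** No dropout; between-visit correlation 0.6 (0.5 and 0.8 also tried); a change of 0 to 0.30 SD common to both arms; no true difference between arms.

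**The plan's own figure.** The 320 is not in dispute here. With 95% power it is approximately reproduced if the effect size of 0.20 is Cohen's f (d = 0.40): 2 × (1.96 + 1.645)² / 0.40² gives 163 per arm, 326 in total. With d = 0.20 the total would be 1300. Nothing below depends on which is meant.

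**One visit pair.** The SD of a change is √(2(1 − 0.6)) = 0.894 SD. With λ = change × √160 / 0.894, the chance that one arm's paired test is significant is p = Φ(λ − 1.96) + Φ(−λ − 1.96). With identical arms, the chance that PCNA is significant and Care-as-Usual is not is p(1 − p). Example at 0.10 SD: λ = 1.41, p = 0.29, p(1 − p) = 0.29 × 0.71 = 0.21. A simulation of 10,000 trials per setting gave:

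| Common change (SD) | PCNA within-arm test significant | Significant in PCNA only | Between-arm test significant |
|---|---|---|---|
| 0 | 5% | 5% | 5% |
| 0.10 | 29% | 21% | 5% |
| 0.15 | 56% | 25% | 5% |
| 0.20 | 81% | 15% | 5% |
| 0.30 | 99% | 1% | 5% |

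Across correlations 0.5, 0.6 and 0.8 the between-arm rate ranged from 4.6% to 5.3%. The PCNA-only rate at 0.10, 0.15 and 0.20 SD was 19%, 25% and 21% with correlation 0.5, and 25%, 13% and 2% with correlation 0.8.

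**Direction.** If the shared change is a decline, the pattern that flatters the intervention is significance in Care-as-Usual only. With identical arms it has the same probability as the PCNA-only pattern.

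**All ten pairs of one outcome (simulated, correlation 0.6).** At least one pair is significant in PCNA only in 29% of trials with no change at all. This rises to 52% and 73% with a linear common change reaching 0.10 and 0.20 SD at month 18.

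**Maintenance read as a non-significant change.** The chance of missing a true decline is 1 − p: 71%, 44% and 19% for declines of 0.10, 0.15 and 0.20 SD.

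**Number of tests.** Leaving out cost measures and items from healthcare professionals, Table 3 has eight patient or caregiver outcomes at five visits and two at four visits (T1 to T4).

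- Named pairs only (four of the six do not involve T0): 8 × 6 × 2 + 2 × 4 × 2 = 96 + 16 = 112; 112 × 0.05 = 5.6.
- All pairs: 8 × 10 × 2 + 2 × 6 × 2 = 160 + 24 = 184; 184 × 0.05 = 9.2.

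So about 6 to 9 within-arm tests would be significant by chance with no change anywhere.

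**The case against.** The strongest reply is that the plan already contains the right analysis. The sentence after the within-arm comparisons introduces the between-arm multilevel model, the paragraph ends with the treatment-by-time interaction, and the sample size rests on the between-arm contrast. That stands, and it limits the point. Several stronger readings that a reader might infer are not supported:

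- *That effects are tested only within arms, or that the trial discards its randomisation.* The within-arm tests ignore randomisation; the plan as a whole does not.
- *That a non-significant PCNA result would be declared success.* No decision rule says so. The hypothesis is a general statement of aims that leaves this reading open.
- *That the later pairs use only patients alive and responding at both visits.* The within-arm method is not named. Complete-case paired tests are possible, but so are time contrasts from the model.
- *That there are at least 184 tests.* That takes the open-ended list to cover every pair; 112 is the count from the named pairs.
- *That the misleading pattern is frequent whatever happens.* For one pair it is about 5% with no common change and 1% at 0.30 SD. It peaks at intermediate changes, and the article gives no expected change.

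It can also be said that a condensed article may leave the ranking of analyses to a fuller document. That is fair for the ranking. It does not cover the point here, which is a stated analysis at a stated threshold and a stated hypothesis without a comparator.

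**Conclusion.** The point holds in limited form. The article plans within-arm significance tests that cannot show a treatment effect, does not label them descriptive, and words its hypothesis in a way that suits them better than the valid model. If the arms do not differ and share a change of 0.10 to 0.20 SD, a single PCNA within-arm test is significant in about 29% to 81% of trials, and in PCNA only in about 15% to 25%. The between-arm test stays near 5%. These rates rest on 160 per arm, correlation 0.6, no dropout and the assumed common change. The principle does not depend on those assumptions.

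The severity is below must-fix, because the between-arm analysis is already planned and is unaffected. This is a cheap improvement that closes a route to a false conclusion.

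**What to change.** 1. In Data management and statistical analysis, replace the within-group comparisons with a descriptive report: means and changes by arm and visit, with 95% CIs and no p-values.
2. In Aims and objectives, restate the patient and caregiver hypotheses as differences between PCNA and Care-as-Usual.
3. State that all conclusions on effectiveness come from the between-arm contrasts of the multilevel model already planned.

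A between-arm margin for a claim of maintenance is optional. It would add a non-inferiority framework that the present aims do not require.

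The cost is a few sentences and somewhat less analysis, with no new data. The only thing lost is the within-arm p-values.

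### Pearson correlation and Pearson chi-square do not fit a continuous score paired with a multi-category characteristic, and neither takes account of site

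*Protocol article*

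**What the plan says.** All of this is in the protocol article.

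- **Association step** (Data management and statistical analysis). "The relationship between the outcome measures and independent variables" "will be assessed using Pearson correlation (for continuous variables) and Pearson Chi-square test (for categorical variables"). No adjustment or stratification is named for this step.
- **Arm comparison** (same paragraph). A multilevel model is specified, "taking into account the clustering effects at the clinical site level", with a group-by-time interaction.
- **Type of outcome.** The sample size is set for an effect "regarding continuous outcome measures between intervention and control group". The analysis section adds: "Tests for normal distribution of the continuous outcome measures will be performed using the Kolmogorov–Smirnov test".
- **Characteristics.** Table 2 lists "Level of education", sex, marital status, ethnic background, professional category and main diagnoses, among others.
- **Sites** (Study setting). Spain recruits multi-morbidity. Greece recruits respiratory disease, heart failure and frailty. Portugal and the UK recruit multi-morbidity or severe COPD.
- **Significance.** The same 0.05 threshold is applied to every analysis.

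**The concern.** There are two faults in one sentence.

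**Test and data do not match.** Pearson correlation needs two numeric variables, and Pearson chi-square needs two categorical ones. A common pairing here is a score (POS, HADS, ZBI, EQ-5D-5L index) against a variable such as marital status, education or diagnosis. The sentence offers no suitable test for it.

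**Site is left out.** Diagnosis is partly set by site, and other characteristics and scores may also differ between countries. A pooled test can then report a difference between countries as a link between a characteristic and an outcome. The plan recognises site clustering for the arm comparison but not here.

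At stake is whether associations called significant at 0.05 are trustworthy, and whether real ones are missed. The Discussion hopes to identify potentially effective elements of early palliative care, so such results could be cited.

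**Working it through.** No figure in the article belongs to this sentence, so there is nothing to reproduce. The inputs taken from it are N = 320, four sites of 80, and alpha 0.05 (taken as two-sided). The effect sizes and intraclass correlations (ICCs) below are assumptions.

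**1. Chi-square on an ungrouped score.** Suppose all 320 values are distinct and the characteristic is binary. The table is then 320 × 2 with one person per row. The statistic equals N whatever the data: 320 on 319 df, p = 0.47. This result appears both with no group difference and with a 2 SD difference. The test is uninformative unless scores are grouped.

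**2. Cost of grouping, if a median split were used.** Take a binary characteristic split 160/160 and a difference d = 0.31.

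- Score kept continuous: d × √(320/4) = 0.31 × 8.94 = 2.77. Power ≈ Φ(2.77 − 1.96) = Φ(0.81) ≈ 79%.
- Median split: difference in proportions = 2Φ(0.155) − 1 = 0.123. Standard error = √(2 × 0.25/160) = 0.0559. Ratio = 2.20. Power ≈ Φ(2.20 − 1.96) ≈ 60%.
- With both margins at 160, chi-square equals k²/20, where k is the excess over 80 in one cell. It crosses 3.84 between k = 8 (3.20) and k = 9 (4.05). The working cut is about 8.5/√20 = 1.90, so power ≈ Φ(0.30) ≈ 62%.

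Simulation agrees: 79-80% against 62-64% at d = 0.31, and 89-90% against 73-76% at d = 0.36. The large-sample efficiency of a median split is 2/π = 0.64, which is like analysing 0.64 × 320 ≈ 205 people.

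**3. Pooled correlation with site ignored.** Outcome and characteristic each get independent site effects, with no association within site. A rough variance inflation for the correlation is 1 + (80 − 1) × ICC of characteristic × ICC of outcome. It depends on the product, so both variables must vary by site. The approximate type I error is 2[1 − Φ(1.96/√inflation)]. This overshoots with only four sites, so the simulated values are the ones to use.

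| ICC, characteristic / outcome | Inflation | Approximate | Simulated, pooled |
|---|---|---|---|
| 0.02 / 0.02 | 1.03 | 5.4% | about 5% |
| 0.05 / 0.05 | 1.20 | 7.3% | 6-7% |
| 0.1 / 0.1 | 1.79 | 14% | 11-12% |
| 0.2 / 0.1 | 2.58 | 22% | 16-18% |
| 0.2 / 0.2 | 4.16 | 34% | 25-27% |

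If the characteristic does not vary by site, simulated error is about 5%. With site adjusted for by indicator variables, it is about 5% in every row.

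**The case against.** The strongest defence is that the step is minor. No objective or hypothesis in the article concerns predictors of outcome, and simple bivariate associations beside a main model are common. The sentence can also be read as matching the test to the pair: correlation for two continuous variables, chi-square for two categorical ones. The mixed pair would then be left to a fuller plan. Categorical outcomes do exist: "Perceived quality of care is assessed through a 5-point Likert scale", and single EQ-5D-5L dimensions could be tabulated.

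This lowers the weight of the point but does not remove it. The phrase about categorical variables naturally covers the categorical items of Table 2. The article also names its methods here rather than deferring them, and neither named method handles site.

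A reader might infer four stronger things that the article does not support:

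- **That scores will be dichotomised.** No grouping is mentioned, so the power loss is conditional on it.
- **That the five visits are pooled in one correlation.** Nothing says so; the article treats time points separately elsewhere.
- **That leaving out arm makes associations spurious.** The Table 2 characteristics come from the baseline questionnaire and are independent of arm by randomisation. Omitting arm adds only residual variance, about d²/4 = 0.2²/4 = 1% for an arm effect of 0.2 SD.
- **That the treatment comparison is compromised.** It uses the multilevel model.

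**Conclusion.** The point holds as a secondary matter worth correcting. The named tests do not suit a continuous score paired with a multi-category characteristic, and they leave out a site structure that the plan itself recognises.

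The power loss, about 80% to 63% at d = 0.31, applies only if scores are split at the median. The excess of false positives applies only if outcome and characteristic both differ by site. It ranges from none (ICCs up to 0.02) to a type I error of about 27% (0.2 for both). The article gives no ICCs. The different case mix makes site confounding plausible but does not size it, so these associations can be spurious but need not be. The randomised between-arm results are unaffected.

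**What to change.** Replace the sentence with wording such as: *Associations between outcomes and patient or caregiver characteristics will be estimated by adding the characteristic as a covariate to the multilevel model used for the arm comparison (site, arm, visit, repeated measures within person). Scores are kept on their original scale, and estimates are reported with 95% confidence intervals. Pearson chi-square is used only where both variables are categorical. Any simple bivariate results are labelled unadjusted and descriptive.*

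The cost is one sentence and slightly more modelling work. The model is already planned and the variables are already collected, so no new data are needed.

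### The protocol does not say how T0 enters the group-by-time model; fitted without a constraint at T0, the model is less precise than baseline adjustment, and two outcomes have no T0 value

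*Protocol article*

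**What the plan says.** All references are to the protocol article.

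- **Between-arm model** (Data management and statistical analysis). A multilevel model accounts for clustering by clinical site. On the arm contrast the section says: "Comparison between the intervention group and the control group at each evaluation moment will be conducted by including an interaction". The interaction meant is that of arm with time. No baseline covariate is named. The section does not say whether T0 is one of the levels of time, or whether the arms share a mean at T0.
- **Within-group comparisons** (same section). Outcomes are compared between pairs of times. The pairs listed include T0-T1 and T0-T4, and no outcome is exempted.
- **Economic analysis** (same section). "The incremental cost-effectiveness ratio (ICER) will be calculated", with non-parametric bootstrapping. Baseline utility and baseline costs are not mentioned.
- **Schedule** (Table 3). T0 is listed for 10 of the 12 patient and caregiver rows, including EQ-5D-5L, MCQ and VICQ. The two exceptions are "Adherence to treatment" (MOS, patients) and caregiver-rated quality of care, both T1 to T4. Patient-rated quality of care does include T0.
- **Sample size** (Sample size considerations). The planned power is 95% and the effect size is 0.20, its metric left unnamed. The section continues: "with an alpha risk of 0.05, the sample size is estimated to be 320 participants". Every site is to contribute "40 participants in the intervention group and 40 in the control group".

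**The concern.** A group-by-time interaction does not by itself use the baseline efficiently. In an unconstrained model with a separate mean for every arm and time, the arm difference at a visit is a follow-up-score comparison, and the interaction term against T0 is a change-score comparison. These give different estimates and p-values from the same data, and the text does not say which one counts. Neither is as precise as conditioning on T0, so information already being collected could go unused.

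The same applies to QALYs and costs. Chance differences between arms in baseline utility or prior care use add avoidable noise to the incremental estimates.

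There is also a mismatch between schedule and analysis. For the two outcomes that start at T1, the listed comparisons with T0 cannot be made, and a baseline that was not collected cannot be recovered later.

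**Working it through.** **Inputs from the protocol article.** Effect size 0.20 (metric not named), alpha 0.05 (sidedness not stated; two-sided used here), power 95%, and 4 × 40 = 160 per arm.

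**Assumed.** Baseline-to-follow-up correlation ρ of 0.3, 0.5 or 0.7, since the documents give none. Equal variance and equal correlation across the five times, complete data, and a model that respects repeated measures within patients.

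**Step 1: the stated sample size.**
- As a standardised mean difference: n per arm = 2(1.960 + 1.645)² / 0.20² ≈ 650, or 1,300 in total. With 160 per arm, power = Φ(0.20 × √(160/2) − 1.960) = Φ(−0.171) = 43%. The stated 320 is not reproduced.
- As Cohen's f = 0.20 (equal to d = 0.40): 2(1.960 + 1.645)² / 0.40² gives 163 per arm, or 326 in total. This is within 3% of 320.
- As a correlation r = 0.20: (1.960 + 1.645)² / atanh(0.20)² + 3 = 319.2, that is 320.

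**Step 2: variance of the arm contrast at T4, relative to an unadjusted follow-up comparison.** The formulas are 1 for the follow-up score, 2(1 − ρ) for change from T0, and 1 − ρ² for baseline adjustment. A generalised least squares calculation for a five-time group-by-time model gave the same values.

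| | ρ = 0.3 | ρ = 0.5 | ρ = 0.7 |
|---|---|---|---|
| Arm difference at T4, unconstrained | 1.00 | 1.00 | 1.00 |
| Interaction, T4 minus T0, unconstrained | 1.40 | 1.00 | 0.60 |
| T0 as covariate, or T0 with a common mean | 0.91 | 0.75 | 0.51 |
| Saving against follow-up score | 9% | 25% | 49% |
| Saving against change score | 35% | 25% | 15% |

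The last row is 1 − 0.91/1.40, 1 − 0.75/1.00 and 1 − 0.51/0.60. Having T0 as a time level does not bring the saving by itself; the common mean at T0 does.

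**Step 3: power if 0.20 is a standardised mean difference.** Power = Φ(0.20 × √80 / √v − 1.960), where v is the variance factor from step 2.

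| | ρ = 0.3 | ρ = 0.5 | ρ = 0.7 |
|---|---|---|---|
| Follow-up score | 43% | 43% | 43% |
| Change score | 33% | 43% | 64% |
| Baseline-adjusted | 47% | 54% | 71% |

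With 320 patients, ρ would have to be about 0.77 for 80% power and 0.87 for 95%. If 0.20 is Cohen's f, unadjusted power is already 94.7%, rising to 98.5% at ρ = 0.5.

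**Step 4: QALYs, for illustration.** Assume a utility SD of 0.25 and a correlation of 0.6. The standard error of the baseline utility difference is 0.25 × √(2/160) = 0.028. Carried over 1.5 years: 0.028 × 0.6 × 1.5 = 0.025 QALY. This is one standard error of chance imbalance, not an expected error.

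**Step 5: Table 3 against the analysis section.** MOS adherence and caregiver-rated quality of care have no T0, while the analysis section lists T0-T1 and T0-T4 without exception. Two further rows lack T0, fidelity and intervention costs. They concern the intervention itself and have no meaningful value before it.

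**The case against.** The best counter-argument is that silence is not a decision. The article neither uses nor rules out baseline adjustment, covariates are commonly left to an analysis plan, and that plan is not shown. A group-by-time model with a common T0 mean fits the wording and loses nothing. This stands: a reader might infer that the trial will not adjust for baseline, and the documents do not support that. What remains is that the article commits to a contrast whose ordinary unconstrained forms are both inefficient, and does not say which form is meant.

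Three other strong readings also fail.

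- **A loss of 25% to 50% of the variance as a fact.** That needs a correlation of about 0.50 to 0.71 and T0 left unused. At 0.3 the figure is 9%, and against change scores it ranges from 35% to 15%.
- **A trial already short of power.** This holds for a standardised mean difference but not for Cohen's f or r. The unnamed metric is a separate issue.
- **A biased QALY difference.** Randomisation gives chance imbalance an expectation of zero, and a bootstrap over patients carries it into the uncertainty around the ICER. Adjustment buys precision.

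On the schedule, the randomised comparisons at T1 to T4 remain valid for the two outcomes, and pairs such as T1-T4 can still be used. That limits the seriousness of the mismatch but does not remove it.

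**Conclusion.** The point holds as one of efficiency and clarity. The role of T0 in the between-arm model is unstated, and baseline adjustment has lower variance than either unconstrained contrast at every correlation tried. The size depends entirely on the assumed correlation. The power gain, at most from 43% to about 71% over 0.3 to 0.7, applies only if 0.20 is a standardised mean difference, and even then falls well short of the stated 95%.

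The mismatch between Table 3 and the listed T0 comparisons is real for two outcomes, and does not rest on any assumption about correlation. The change is worth making, but no result would be invalid without it.

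**What to change.** 1. State how T0 enters the model. Either take T1 to T4 as outcomes, with the T0 value (by time) and site as covariates, or include T0 as a response with a common mean in both arms. Say which contrast is reported.
2. Within each bootstrap sample, regress QALYs on baseline utility and costs on baseline MCQ and VICQ costs. Describe this as a gain in precision.
3. For MOS adherence and caregiver-rated quality of care, either add T0 to Table 3 for participants not yet enrolled, or exempt both outcomes from the comparisons with T0 and say that they are analysed from T1 without baseline adjustment.

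The first two cost a few sentences in the analysis plan and need no new data. Adding T0 in the third costs two short item sets in the baseline questionnaire, and participants already enrolled would still lack the value. The exemption costs only wording.
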